## Abstract

**Background:**

Basic life support (BLS) skills are crucial not only for healthcare workers but for all lay people as well. Timely recognition of out-of-hospital cardiac arrest (OHCA) and the initiation of BLS by bystanders before the arrival of healthcare personnel may improve survival. There are several methods of spreading BLS skills and improve BLS skill retention among lay people. One of these methods can be the education of adolescent school children. The introduction of mandatory BLS education in schools was very effective in some European countries to increase the rate of bystander BLS.

**Methods/design:**

The current study aims to investigate the efficacy of a BLS training and BLS curriculum among high school children in Hungary. Moreover, the investigators would like to optimise factors influencing skill retention in this first responder group and aim to compare two types of teaching methods: feedback given by the instructor or software-based feedback on the efficacy of chest compressions during the course. This study will be an interventional, assessor blinded, individually randomised parallel group trial recruiting 360 students. BLS skill retention will be assessed at the end of the course, two months after the training and six months after training.

**Discussion:**

The current study will increase our knowledge on the methods educating BLS among high school children. The results will help us to create an effective BLS curriculum at schools.

**Trial registration:** ClinicalTrials.gov: NCT06016153. Prospectively registered on 08/2023.

## Introduction

Sudden cardiac death is one of the most common causes of death in Europe.^1^ Despite the great efforts we have made in the past decades to increase the effectiveness of resuscitation survival rate is still poor. Average, 350,000–700,000 people suffer from out-of-hospital cardiac arrest (OHCA) in Europe, from which resuscitation takes place approximately in 100,000 cases and spontaneous return of circulation could be achieved only in 40,000 cases. Only 3% of all patients who suffered OHCA survive permanently without any impairment of quality of life (Cerebral Performance Category 1).^2^, ^3^

The elements of the survival chain (early recognition of cardiac arrest and immediate call for help, chest compression started as early as possible, early defibrillation (if appropriate), and adequate post resuscitation care) determine the good outcome of cardiopulmonary resuscitation. The chain is as strong as its weakest link; therefore, it is mandatory to enforce all the links that is based on well-established educational and training methods.^4^

The first two links of the chain define the effectiveness of basic life support (BLS), consequently the high quality BLS is the first and very important key that improves the outcome of OHCA patients. However, BLS provider skills deteriorate three to twelve months after learning the BLS procedure if it has not had been applied or practiced during this period of time.^5^, ^6^ Several tools and methods have been investigated previously to improve BLS skill retention. One of them is the usage of systems and tools that reflect the effectiveness of the elements of BLS applied during the process.^7^, ^8^ The application of feedback devices is also beneficial giving an immediate response on the quality of BLS to the provider, so inappropriate action and technical elements, such as the depth and frequency of chest compressions, can be revised and corrected continuously and the chance of return of spontaneous circulation can be improved. However, we would like to point out that the positive effect of feedback devices on survival rates has not yet been proven.^9^ On the other hand, several other educational methods have been also investigated to improve BLS skill retention. It has been proven that taking exam at the end of the BLS practice is more effective than if the students spend the same amount of time with practicing. Nevertheless, it is not clear whether the timing of the exam, namely the duration between the practice and the exam affects skill retention.^10^

In addition, the early education of children and adolescents for BLS is getting highly emphasized in the recent scientific position statements from the European Resuscitation Council (ERC) and International Liaison Committee on Resuscitation (ILCOR).^11^ Young people are important target for BLS education based on its multiple effects. Beside that they can act as multipliers and transmitters of the specific information concerning BLS to their environment, all groups of society could be reached via them. For the distribution of early age provider BLS, “Kids Save Lives” program was launched by the ERC in 2015. Providing resuscitation training in schools (from the age of 12, two hours per year) is one of the most important steps in increasing the rate of bystanders and improving the worldwide survival.^12^, ^13^

We must highlight that the result of an effective BLS education should be the ability to provide high-quality chest compression.

### Aims and objectives

The current study aims to investigate the efficacy of a BLS training and BLS curriculum among 16–19 year old high school adolescence in Hungary. By investigation of the factors influencing short- and long-term skill retention in this age group we aim to compare two types of teaching methods: the feedback concerning the efficacy and quality of chest compression is given by an experienced instructor or by a real-time software during the BLS training. The trial also wants to determine whether the motivation of the students affects BLS skill retention or not.

## Methods

### Design

The trial is an anonymous, interventional, prospective longitudinal, assessor blinded, individually randomised, parallel 1:1 grouped trial to determine and compare the efficiency of the two teaching methods: feedback given by the instructor or by a software and CPR-sensor module on the efficacy and quality of chest compressions during the course. This protocol has been written in concordance with the SPIRIT guidelines (Table 1 and Appendix 1).^14^

**Table 1 t0005:** Trial registration data set (BLS: Basic Life Support).

Data category	Information
Registry	ClinicalTrials.gov ID: NCT06016153
Date of registration	08/2023
Human Subjects Review	Board Status: Approved Approval Number: 160/2023 Board Name: Semmelweis University Regional and Institutional Committee of Science and Research Ethics Board Affiliation: Semmelweis University Email: [contact] Address: [name]
Primary sponsor	Semmelweis University This funding source had no role in the design of this study and will not have any role during its execution, analyses, interpretation of the data, or decision to submit results.
Secondary sponsor	none
Central Contact Person	[name] [contact]
Central Contact Backup	[name] PhD [contact]
Study Officials	[name] PhD Study Principal Investigator, Semmelweis University
Public Title	The Efficacy of Basic Life Support Education Among Teenagers
Scientific Title	The Investigation of the Efficacy of Basic Life Support Education Among High School Students
Countries of recruitment	Hungary
Health condition(s) or problem(s) studied	The quality of Basic Life Support
Intervetion(s)	BLS training, feedback given by the instructor or a CPR analyser software
Key inclusion criteria	• High school teenagers (aged 16–19 years) participating in the education of Óbudai High School, Budapest • Written informed consent received from participants and their parents to participate in the study
Key exclusion criteria	• Missing written informed consent provided by the student or parent • Any injury or health issue influencing the efficacy of BLS skill
Study type	• Study Type: Interventional • Interventional Study Model: Parallel Assignment • Number of Arms: 2 • Masking: Single (Outcomes Assessor) • Allocation: Randomized
Date of first enrolment	December 2023
Target sample size	360
Recruitment status	Recruiting
Primary outcome(s)	Results of the assessment at the end of the training
Key secondary outcome(s)	Results of the assessments two and six months after the training

In addition, a questionnaire will be used to collect data on students’ characteristics and motivation (see Appendix 2).

The Semmelweis University Regional and Institutional Committee of Science and Research Ethics approved our study (Approval number 160/2023). In the case of any protocol modifications, the Board will be notified by author EZ via email and official letter.

### Setting, criteria

#### Participants

The research focuses on students aged between 16 and 19 years from a secondary school in Budapest (Óbudai High School). We plan a pilot study from the results of the first 60 schoolchildren to be able to make a power analysis and an effect size.

The main trial is planned to involve 330–360 students. If necessary, we will consider to involve more high schools to participate.

A written informed consent provided from the participants and their parents is needed to participate in the study before any trial procedures occur (see Appendix 3 for a sample of the written informed consent form). The text of the consent will be sent out before the study to participants and the written formats will be collected by instructors on-site, at the beginning of trainings. In addition, students will need to fill out a brief questionnaire about their basic characteristics and future educational motivation (gender, age, prior participation in BLS course, plans about future specialisation, etc). The participation in the study will be voluntary. Students can indicate any time their withdrawal from the trial.

Student eligibility for the trial must comply with all the criteria listed and reviewed in Table 2.

**Table 2 t0010:** Inclusion and exclusion criteria (BLS: Basic Life Support).

*Inclusion criteria*	*Exclusion criteria*
High school teenagers participating in the education of Óbudai High School, Budapest	No written informed consent provided by the student and/or parent. Unwilling to participate on site
Written informed consent received from participants and their parents to participate in the study	Any injury or health issue influencing the efficacy of BLS performance

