#### Randomisation

Students will be simply randomised in two groups by randomly dividing the groups. Participants randomised to **Instructor Group** will take part in a 90-minute-long BLS training and get a feedback based on the own experience of the instructor. Students randomised to **Software Group** will also take part in a 90-minute-long BLS training, but they will receive feedback by a real-time software-based feedback system (Ambu Man model C Manikin, Ambu A/S, Ballerup, Danish Kingdom, and InnoMed CardioAid-1 Trainer AED, Innomed Inc., Budapest, Hungary). There will be four BLS training occasions for the 360 students organized during school time with the help of teachers. Students applying for the first two occasions of the trainings will be randomised to Instructor Group and students applying to the last two occasions will be randomised to Software Group. Two authors (CsM and EZ) will be responsible for the randomisation and students’ enrolment to the study. All students will receive a code that will be added to a Microsoft Excel spreadsheet (Microsoft Corporation, Redmond, WA) with the name and grouping information of the students. To secure students’ anonymity, only the codes will be used during the evaluation and data process. Due to the nature of the study and intervention students and instructors will know which group they belong to during the trainings. Skill retention assessment with an observational checklist will be performed at the end of the training, two months later and six months later by our instructors to evaluate short- and long-term BLS skill retention. All data regarding the students’ performance will be added to another Microsoft Excel spreadsheet. The instructors will be blinded during skill retention assessment and will not be aware of student grouping. The assessor instructors will be independent from the instructors educating during the trainings. Fig. 1 summarizes the flow of the trial.

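### Consent forms and willingness are settled on the training day, after the occasion has set the arm, and a student who declines is classed as ineligible rather than as a loss from that arm

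*Protocol article*

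**What the plan says.** All references are to the protocol article, Methods.

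- **Arm.** The Design section describes individual 1:1 randomisation. The Randomisation section, however, sends students who sign up for the first two of four training occasions to the Instructor Group and those who sign up for the last two to the Software Group.
- **Consent.** Under Participants, consent of student and parent is required "before any trial procedures occur". "The text of the consent will be sent out before the study to participants", but the signed forms "will be collected by instructors on-site, at the beginning of trainings".
- **Exclusions.** Table 2 lists absence of a signed form, being "Unwilling to participate on site", and an injury or health problem that would affect performance.
- **Withdrawal.** Participants separately allows a student to withdraw at any time.
- **Blinding.** The Randomisation section says that "students and instructors will know which group they belong to during the trainings".
- **Missing data.** Under Statistical analysis, up to 5% missing data are left out, and above 5% multiple imputation is used. The rule does not mention excluded students.

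**The concern.** In a randomised comparison, eligibility and consent should be closed before the arm is set, so that nothing about the arm can influence who is in the trial. Here two of the entry conditions, handing in the form and being willing on the day, are closed afterwards, in a session whose arm is already set.

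If willingness on the day differs between occasions and is related to interest or ability, the students who stay are no longer comparable across arms. The reason could be the feedback method or something that goes with the occasion, such as the timetable. The end-of-training skill score, which is the primary outcome, would then carry that difference. Because Table 2 makes such a student ineligible, the plan as worded gives no reason to keep that student in the arm's denominator or to treat the absent score as missing.

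**Working it through.** **Order of events.** Set side by side, the sections give this sequence:

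1. The consent text is sent out before the study.
2. The student signs up for an occasion, and the occasion sets the arm.
3. At the start of that session the instructors collect the signed forms.
4. A student without a form, or unwilling on site, is excluded under Table 2.
5. Training and the primary assessment follow.

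Steps 3 and 4 come after step 2. The position of step 1 relative to step 2 is not stated. Nor is the time at which injury or health problems are checked, so that criterion cannot be placed in the sequence.

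**Size.** The plan has no figure to reproduce: it gives no refusal rate, SD or effect size. The following is illustration only.

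Inputs:
- From the document: 360 students in two arms at 1:1, so 180 per arm, and a significance level of 0.05.
- Assumed: a two-sided test, no true effect, outcome SD of 1, refusal shares r1 and r2, and a gap g (in SD) between the scores of stayers and the scores that refusers would have had.

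Formulas:
- The stayers' mean exceeds the whole-arm mean by r × g, so the bias in the arm difference is g × (r2 − r1).
- SE = √[1/(180(1 − r1)) + 1/(180(1 − r2))].
- Type I error = P(Z > 1.96 − bias/SE) + P(Z < −1.96 − bias/SE).

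| r1 v r2 | g | Bias (SD) | SE (SD) | Bias/SE | Type I error |
|---|---|---|---|---|---|
| 2% v 10% | 0.5 | 0.5 × 0.08 = 0.04 | √(1/176.4 + 1/162) = 0.109 | 0.37 | 6.6% |
| 2% v 15% | 0.5 | 0.5 × 0.13 = 0.065 | √(1/176.4 + 1/153) = 0.110 | 0.59 | 9.0% |
| 5% v 20% | 0.8 | 0.8 × 0.15 = 0.12 | √(1/171 + 1/144) = 0.113 | 1.06 | 18.6% |

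A second set of assumptions puts refusal in one arm only, with r from 5% to 20% and g from 0.3 to 1.0 SD. The bias then runs from 0.015 to 0.20 SD and the type I error from 5.2% to 43%.

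For scale, 180 per arm detects (1.96 + 0.84) × √(2/180) = 0.295 SD at an assumed 80% power. A bias of 0.04 SD is about one seventh of that, and 0.12 SD about two fifths.

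**Effect of the label.** In the first row, refusers would be (0.02 × 180 + 0.10 × 180)/360 = 21.6/360 = 6% of those allocated. If the plan's 5% threshold is read as the share of allocated students without a primary score, counting them as missing would call for multiple imputation. Counting them as ineligible would not.

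**The case against.** Several objections limit the point.

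- **Collecting a form is not the same as deciding.** The consent text goes out in advance and nothing says that parents attend, so many decisions may be made before the day. This stands. Only unwillingness on site is clearly an on-the-day decision. For consent, what is settled on the day is the handing in of the form.
- **Knowledge of the arm.** A reader might infer that students refuse knowing their arm. The document says that they know it during the trainings, not when they hand in the form. The instructors who collect the forms do run a session whose arm is set, and refusal can differ by occasion without any knowledge of the feedback method.
- **All exclusions after allocation.** A reader might infer this for the injury and health criterion too. No section says when it is checked.
- **Losses hidden from the report.** A reader might infer that refusers will go unreported. No section says so. Fig. 1, the flow diagram, is not shown, and reporting of exclusions may sit in a fuller document. What can be said is that the eligibility criterion itself removes these students from the arm.
- **Overlap with the allocation rule.** The order problem arises here because the occasion sets the arm, and self-selection of occasion is probably the larger source of bias. An individual random draw made after consent would largely remove the problem, but a random list drawn before the forms come in would not. The two corrections belong together.
- **Weak supporting points.** Table 1 lists only key exclusion criteria, so its shorter list is no contradiction. Consent does precede training and assessment. The requirement that it come before trial procedures is strained only if setting the arm counts as one.
- **No evidence of differential refusal.** Both arms receive a 90-minute session in school time with largely the same content. The document gives no reason to expect a large imbalance, and a small one does little harm.

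**Conclusion.** The point holds in a limited form. By the document's own wording, form collection and willingness are settled after the occasion has set the arm, and a student who declines on the day is classed as ineligible. That leaves a route for arm-dependent selection in the primary comparison which the plan does not need to leave open.

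The size and direction are unknown, and every refusal share and gap used above is assumed. Modest imbalance matters little (0.04 SD, type I error about 6.6%). The comparison is seriously affected only if refusal is both unequal between arms and strongly related to performance (for example 0.12 SD and about 19%). The document does not show that such refusal will occur. The case for amending rests on the low cost of closing the route, not on a demonstrated bias.

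**What to change.** 1. Collect student and parent forms through the school, and apply the Table 2 criteria, including the health check, before allocation.
2. Allocate only consented and eligible students. Make this change together with the correction of the occasion-based allocation in the Randomisation section.
3. Delete on-site unwillingness from the exclusion criteria. Students keep the right to decline, since Participants already allows withdrawal at any time. Only the accounting changes.
4. Count any refusal after allocation as a withdrawal or missing outcome in the allocated arm, report the numbers by arm, and bring them under the missing-data rule.

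The cost is an earlier deadline for forms and a short amendment to Participants and Table 2. The advance mailing of the consent text already supports the earlier deadline. The downside is that a student who brings the form only on the day can be trained but is not counted in the trial. Step 4 does not recover the missing scores. It makes the loss visible and open to the missing-data analysis.

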#### Randomisation

Students will be simply randomised in two groups by randomly dividing the groups. Participants randomised to **Instructor Group** will take part in a 90-minute-long BLS training and get a feedback based on the own experience of the instructor. Students randomised to **Software Group** will also take part in a 90-minute-long BLS training, but they will receive feedback by a real-time software-based feedback system (Ambu Man model C Manikin, Ambu A/S, Ballerup, Danish Kingdom, and InnoMed CardioAid-1 Trainer AED, Innomed Inc., Budapest, Hungary). There will be four BLS training occasions for the 360 students organized during school time with the help of teachers. Students applying for the first two occasions of the trainings will be randomised to Instructor Group and students applying to the last two occasions will be randomised to Software Group. Two authors (CsM and EZ) will be responsible for the randomisation and students’ enrolment to the study. All students will receive a code that will be added to a Microsoft Excel spreadsheet (Microsoft Corporation, Redmond, WA) with the name and grouping information of the students. To secure students’ anonymity, only the codes will be used during the evaluation and data process. Due to the nature of the study and intervention students and instructors will know which group they belong to during the trainings. Skill retention assessment with an observational checklist will be performed at the end of the training, two months later and six months later by our instructors to evaluate short- and long-term BLS skill retention. All data regarding the students’ performance will be added to another Microsoft Excel spreadsheet. The instructors will be blinded during skill retention assessment and will not be aware of student grouping. The assessor instructors will be independent from the instructors educating during the trainings. Fig. 1 summarizes the flow of the trial.

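### The arm is set by the training occasion a student applies for, so the trial is not individually randomised and arm cannot be separated from occasion and calendar order

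*Protocol article*

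**What the plan says.** The abstract (Methods/design) describes an "assessor blinded, individually randomised parallel group trial recruiting 360 students", and the Design section an "assessor blinded, individually randomised, parallel 1:1 grouped trial". The Randomisation section begins in the same spirit: "Students will be simply randomised in two groups by randomly dividing the groups".

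The same section then says how this will be done. All 360 are to be taught in four sessions held in school hours. For the earlier pair of sessions the rule reads: "Students applying for the first two occasions of the trainings will be randomised to Instructor Group". Applicants for the later pair go to the Software arm by the same logic. Two of the authors "will be responsible for the randomisation and students’ enrolment to the study".

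Under Participants, the consent text goes out in advance, but "the written formats will be collected by instructors on-site, at the beginning of trainings". Table 2 lists unwillingness to take part on the day as an exclusion. The Statistical analysis section compares the arms by t-test, Mann-Whitney test or chi-square test, with students as the units and no term for occasion.

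**The concern.** The declared design and the working rule cannot both be true. Under the rule, a student's arm follows from the occasion applied for, and all Instructor sessions come before all Software sessions.

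Three consequences follow if the rule is used as written:

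- **Confounding.** Any difference between early and late applicants, any change in how instructors teach as sessions go by, and any incident at one session all load onto the comparison of feedback methods.
- **No concealment from those who enrol.** The arm of every occasion is known beforehand to the two people who both enrol and allocate. The signed forms are handed in at a session whose arm is already settled.
- **Weaker blinding.** The primary outcome is measured at the end of training, when everyone present is in the same arm. An assessor who knows the order of the occasions can infer the arm.

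The aim of the trial is to compare two teaching methods. A difference found this way could not be credited to the feedback method.

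**Working it through.** **1. The text side by side.** Abstract and Design: individual randomisation. Randomisation, opening sentence: simple randomisation into two groups. Randomisation, working rule: occasions 1 and 2 are Instructor, occasions 3 and 4 are Software, by application. Only the last of these says what will be done, and it contains no random draw.

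**2. Structure.** Inputs from the Randomisation section: 360 students, 4 occasions, 2 occasions per arm.

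- Students per occasion, if equal: 360/4 = 90.
- Occasions containing both arms: none. There is no within-occasion contrast between the methods.
- Occasion-level degrees of freedom: 4 − 2 = 2, so the two-sided 5% critical t is 4.30 instead of 1.96.
- Had the two Instructor occasions been drawn at random, there would be C(4,2) = 6 possible allocations, and the smallest two-sided permutation p-value would be 2/6 = 0.33. In fact the order is fixed, so not even this draw takes place.

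**3. Effect on the planned test (illustration).** The protocol article gives no power, effect size or standard deviation, so there is no stated figure to reproduce. It gives no intra-occasion correlation (ICC) either; the values below are assumptions. Two-sided testing at 0.05 is also assumed, because the article states only the level.

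Formulas, with m = 90: design effect DE = 1 + (m − 1) × ICC; effective sample size = 360/DE; actual type I error of the student-level test = 2 × (1 − Φ(1.96/√DE)).

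| Assumed ICC | DE | Effective N | Type I error |
|---|---|---|---|
| 0 | 1.00 | 360 | 5% |
| 0.01 | 1 + 89 × 0.01 = 1.89 | 190 | 15% |
| 0.02 | 1 + 89 × 0.02 = 2.78 | 129 | 24% |
| 0.05 | 1 + 89 × 0.05 = 5.45 | 66 | 40% |
| 0.10 | 1 + 89 × 0.10 = 9.90 | 36 | 53% |

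This table treats occasion effects as random with mean zero. A systematic difference between early and late occasions, or between early and late applicants, is a bias on top of this and does not shrink as more students are added.

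**4. What true individual randomisation would give.** With 180 per arm and no tie between arm and occasion, the standardised difference detectable with 80% power is (1.960 + 0.842) × √(2/180) = 0.295. With 165 per arm, the lower end of the planned size, it is 0.308.

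**5. Knock-on for the pilot.** The Participants section plans to take the power analysis and effect size from the first 60 students. If those 60 come from these occasions, they fit inside the first one (60 < 90). All would then be Instructor students, and no between-arm effect could be estimated.

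**The case against.** The fairest counter-reading starts from the opening sentence of the Randomisation section: students are divided at random first, and each group is then sent to its occasions. This would remove self-selection. It sits badly with the wording that students apply for occasions, and it leaves every Instructor student trained early and every Software student late, so the confounding with occasion and period stays.

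Several other points have substance:

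- **Self-selection is an inference.** The article does not say how far students or teachers choose the occasion, how far apart the occasions are, or whether students know the arm when they consent. Nor does it say when any added schools would train. The conclusion does not need any of these.
- **The ICC is unknown and may be zero.** Four is the number of units allocated, not the effective sample size. Teaching is at about one instructor to six students, so some clustering may sit in the practice group. With m = 6 and an ICC of 0.05, DE = 1 + 5 × 0.05 = 1.25 and the type I error is 2 × (1 − Φ(1.96/√1.25)), about 8%. The table is therefore illustrative only.
- **There are safeguards.** Instructors had standardised pre-training, assessors are separate from teachers, compression rate and depth are device-measured, and age, prior training and career plans are recorded. These limit drift and allow some adjustment for measured differences. They do not separate arm from occasion.
- **Separate occasions reduce contamination** within one school. That is a real reason for the arrangement, but not a reason to call it individual randomisation.

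**Conclusion.** The concern holds. The protocol article contradicts itself on allocation, and its only working rule is deterministic: arm is completely aliased with early versus late training, over two occasions per arm. This follows from the text and rests on no assumed figure. The inflation of type I error to 15%, 24% or 40% depends on assumed ICCs of 0.01, 0.02 or 0.05 at occasion level, and there is none at zero; even then, a period or selection difference would bias the comparison. Self-selection is likely under a rule based on application, but is not established. As written, the trial cannot support a causal statement about feedback method, and its published design label is inaccurate. This must be corrected.

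**What to change.** **If training has not yet been run under the rule:**

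- Collect student and parent consent before allocation.
- Have someone not involved in enrolment randomise consented students 1:1 from a concealed, computer-generated list, stratified by occasion. Disclose the arm only after consent.
- Run both arms in parallel at each of the four occasions, in separate rooms. At 1:6, a 90-student occasion has about 90/6 = 15 practice groups, so 7 or 8 groups per arm.
- Delete the rule that ties the first two and last two occasions to arms, and include occasion in the between-arm analysis.

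The cost is a protocol amendment, a new timetable, two set-ups per occasion and separate rooms. Students, instructors and the number of occasions stay the same, and about 45 rather than 90 students need feedback devices at a time. The price is some risk of contamination between arms on the same day.

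**If sessions have already been run under the rule** (Table 1 gives first enrolment in December 2023 and status recruiting): withdraw the description as individually randomised in the article and the registration, report a non-randomised comparison allocated by occasion, and state that the effect of feedback cannot be separated from occasion and period. Adjustment for age, prior training and career plans is worth doing but does not repair this. The cost is a change of wording and a weaker claim.
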